## Abstract

**Background:**

Influenza-related global deaths reach 650,000 annually. The current highly lethal clinical subtype of influenza is severe influenza.

**Aim:**

To develop and validate a deep learning based model for early diagnosis of severe influenza.

**Methods:**

This is a multi-centre, double-blind, multi-stage, randomised controlled clinical trial. We initially developed a framework for a 5-phase study: model development, external validation, multi-reader study, randomised controlled trial and prospective validation. The data source for the preview programme is electronic health record data from 87 hospitals in Jiangsu Province from 2019 to 2025.

**Significance:**

Our expected result is that the developed model of severe influenza can be more accurate and have a lower misdiagnosis rate than traditional clinical assessment. The pre-specified AUC was 0.18 (95% CI: 0.14-0.22), with an expected 32% reduction in misdiagnosis. The model’s performance was consistent across patients in older adults, underlying disease, and resource-poor areas. The added value of the study is that it is effective in improving early recognition of severe influenza.

**Ethics and dissemination:**

This study was approved by the Institutional Review Board of Yangzhou University Hospital (IRB No. YKL08-002). Written informed consent was obtained from all participants. The results of this study will be disseminated in the form of a conference in the Jiangsu Province area, which will facilitate the translation of clinical research results and provide a powerful decision-making tool for the precise prevention and control of severe influenza.

**Clinical trial number:**

https://clinicaltrials.gov/, identifier (ChiCTR2000028883).

## Introduction

1

Influenza causes 650,000 deaths annually and remains a threat to global health. Influenza has a mortality rate of approximately 20 per cent, and deaths due to influenza predominantly occur among infants, pregnant women, the elderly and the immunocompromised (1, 2). Although progress has been made with previously developed predictive tools and antiviral therapies, this has not reduced mortality from severe influenza (3). A key issue is the dynamic gap between clinical decision-making and risk of severe influenza. Evidence suggests that physicians are overconfident in the outcome of subjective clinical assessments leading to misdiagnosis and quality delays in severe influenza. Another factor, of course, arises from differences in the definition of ‘cure’ in the healthcare system (4, 5). A study by Valenzuela-Sánchez et al. (2024) reported that 34% of severe influenza cases were initially incorrectly classified as mild. The reason for this was an over-reliance on non-specific symptoms by clinicians when assessing influenza (6). This result implies that we need more objective and accurate tools to improve the accuracy of clinical judgement.

Artificial Intelligence (AI) can learn deeply from human health data so that closed-source predictive models can be constructed to identify high-risk patients. The current intersection of AI and healthcare data has shown revolutionary potential (7, 8). Yang et al. (2023) developed an influenza prognostic AI model using only city-scale data, which has achieved a performance AUC value of 0.89 (9). Of course, the lack of external validation of models constructed using AI across regions and healthcare resources means that more effort is needed for AI to address real-world clinical work (10). Dai et al. (2024) concluded that constructed AI diagnostic tools do not work well when put into prospective clinical practice due to population heterogeneity and data drift (11). This may be due to the lack of research-oriented personnel in the field of AI, leaving little understanding of dynamic risk prediction in high-risk subgroups in a clinical context (12).

The aim of our research is to develop and validate a deep learning-based diagnostic model for severe influenza. In order to be able to specify the research tasks at each stage, we established a methodological framework.

Data: data were obtained from 87 hospitals in Jiangsu Province, China. The data features of interest were clinical information, laboratory test results, and demographic information.Stages: 5 research phases with model building, internal validation, comparative study, randomised trial, and prospective real-world validation.Collaboration: the aim of the model is to assist clinicians in accurately identifying patients with severe influenza.

We hypothesize that this model will significantly improve AUC (*Δ* > 0.15) compared to physician-only assessments, reduce misdiagnosis rates by ≥30%, and maintain robustness across hospitals with varying resource levels. By addressing both algorithmic and human factors, this research seeks to establish a scalable solution for mitigating influenza-related mortality, particularly in resource-constrained settings.

## Methods

2

### Study setting

2.1

[name] of the Affiliated Hospital of Yangzhou University proposed the research concept of stratified prevention of severe influenza in 2019, and this was subsequently supported by [name] of Northwest Minzu University in October 2022.

This is a multi-center, multi-phase clinical trial. The study will be conducted across 87 tertiary general hospitals in all prefecture-level cities of Jiangsu Province, China. This study is a continuation of the 2019 investigation of influenza A (ChiCTR2000028883) and is registered on the Open Science Framework (OSF) registry platform (13). This clinical trial will be reported according to Standard Protocol Items Recommendations for Interventional Trials (SPIRIT) 2013 standard specifications (14).

#### Hospital inclusion criteria

2.1.1

We have pre-set criteria for hospital eligibility for the study. Hospitals must be accredited tertiary general hospitals, which provide full emergency and inpatient services. Hospitals should have at least 100 patients with influenza diagnosed by laboratory testing between 2021 and 2023. Hospital clinicians must use electronic health records (EHRs) so that symptoms of influenza patients and other information used for clinical research can be recorded in a standardised format. Longitudinal, anonymous data sharing programmes must be in place within hospitals to ensure the security of patient and clinician information.

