#### Phase I: model development and internal validation

2.3.1

This phase utilizes retrospective EHRs from 87 hospitals (Table 1) in Jiangsu Province (from January 2019 to December 2024), encompassing four key data categories:

Demographics: age, sex, vaccination history, and comorbidities.Clinical symptoms: fever duration, cough frequency, dyspnea severity, and other symptoms detailed (Table 2).Laboratory/imaging data: viral subtype (confirmed via RT-PCR), blood cell counts, and chest X-ray/computed tomography (CT) findings.Outcomes: severe influenza progression and mortality, defined as intensive care unit (ICU) admission or mechanical ventilation.

**Table 1 tab1:** Datasets distribution.

City	Hospitals
Nanjing	Jiangsu Provincial People’s Hospital, General Hospital of the Eastern Theater Command, Nanjing Drum Tower Hospital, Jiangsu Provincial Hospital of Traditional Chinese Medicine, Zhongda Hospital Affiliated to Southeast University, Nanjing First Hospital, The Second Affiliated Hospital of Nanjing Medical University, Nanjing Hospital of Traditional Chinese Medicine
Wuxi	Wuxi People’s Hospital, The Affiliated Hospital of Jiangnan University, Wuxi Hospital of Traditional Chinese Medicine
Xuzhou	The Affiliated Hospital of Xuzhou Medical University, Xuzhou Central Hospital, Xuzhou First People’s Hospital, Xuzhou Mining Group General Hospital, Xuzhou Hospital of Traditional Chinese Medicine
Changzhou	Changzhou First People’s Hospital, Changzhou Hospital of Traditional Chinese Medicine, The Third Affiliated Hospital of Soochow University (Changzhou Second People’s Hospital)
Suzhou	The First Affiliated Hospital of Soochow University, The Second Affiliated Hospital of Soochow University, Suzhou Municipal Hospital, Suzhou Hospital of Traditional Chinese Medicine
Nantong	The Affiliated Hospital of Nantong University, Nantong First People’s Hospital, Nantong Hospital of Traditional Chinese Medicine
Lianyungang	Lianyungang First People’s Hospital, Lianyungang Hospital of Traditional Chinese Medicine, Lianyungang Second People’s Hospital
Huai’an	Huai’an First People’s Hospital, Huai’an Second People’s Hospital, Huai’an Hospital of Traditional Chinese Medicine
Yancheng	Yancheng First People’s Hospital, Yancheng Hospital of Traditional Chinese Medicine, Yancheng Third People’s Hospital
Yangzhou	Subei People’s Hospital, Yangzhou First People’s Hospital, Yangzhou Hospital of Traditional Chinese Medicine

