#### Subgroup analyses

2.4.3

Predefined subgroup analyses will assess heterogeneity in model performance across key variables to evaluate the impact of local healthcare infrastructure and influenza epidemiology.

patient characteristics: age (infants, children, adults, older adults), comorbidities (cardiovascular disease, diabetes), and vaccination status (yes, no);clinician factors: experience level (resident, attending, chief physician);hospital resource tier: urban or rural facilities;geographic variation: northern or southern regions of Jiangsu Province.

These analyses aim to identify subgroups where the model excels or underperforms, informing targeted clinical deployment. Statistical adjustments, such as Bonferroni correction for multiple comparisons and multivariable regression for confounders, will ensure robust interpretation of subgroup differences.

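### Sites and clinicians are limited to tertiary general hospitals, so an urban/rural comparison cannot support claims about resource-poor settings; separately, Table 1 names 46 hospitals, not 87.

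*Protocol article*

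**What the plan says.** **Who may take part.** Section 2.1.1 of the protocol article sets the hospital criteria: "Hospitals must be accredited tertiary general hospitals, which provide full emergency and inpatient services". It adds electronic health records, a data-sharing programme and a volume requirement: "Hospitals should have at least 100 patients with influenza diagnosed by laboratory testing between 2021 and 2023". Section 2.2.3 admits only clinicians who practise in a tertiary general hospital in the province. Section 2.1 describes the setting: "The study will be conducted across 87 tertiary general hospitals in all prefecture-level cities of Jiangsu Province, China".

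**What is to be concluded.** The Introduction hypothesises that the model will "maintain robustness across hospitals with varying resource levels", and its next sentence names resource-constrained settings as a particular purpose. Section 2.1.2 presents the multicentre design as a way to address healthcare inequality between city and countryside. The abstract, under Significance, describes performance as "consistent across patients in older adults, underlying disease, and resource-poor areas".

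**How resources are measured.** The only marker is urban versus rural. It is a randomisation stratum (2.3.4 and 2.6.1), a stratum of the clinician sample (2.5.3) and a subgroup, listed in 2.4.3 as "hospital resource tier: urban or rural facilities" and repeated in 2.8.3.

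**The site list.** Section 2.3.1 states: "This phase utilizes retrospective EHRs from 87 hospitals (Table 1) in Jiangsu Province".

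**The concern.** The eligibility rules select one level of the hospital system, while the hypothesis and the abstract speak about levels below it. Calling the urban/rural split a resource tier hides this, because by the entry criteria every site has the same accreditation tier. If urban and rural tertiary hospitals gave similar results, the trial could be read as showing that the model works in resource-poor facilities, although none of a lower tier had been sampled.

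The site count matters for a second reason. Section 2.1.2 rests its claim of general applicability on having included every eligible hospital in the province. If the list and the count disagree, the reader cannot tell which set of hospitals that claim refers to.

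**Working it through.** **1. The site count.** The plan's figure is 87. Counting names in Table 1 by city:

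| City | Hospitals |
|---|---|
| Nanjing | 8 |
| Wuxi | 3 |
| Xuzhou | 5 |
| Changzhou | 3 |
| Suzhou | 4 |
| Nantong | 3 |
| Lianyungang | 3 |
| Huai'an | 3 |
| Yancheng | 3 |
| Yangzhou | 3 |
| Zhenjiang | 3 |
| Taizhou | 3 |
| Suqian | 2 |
| **Total** | **46** |

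87 − 46 = 41, and 41/87 = 47%. The figure of 87 is not reproduced.

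**2. Eligibility against claim.** No arithmetic is needed. Sections 2.1.1 and 2.2.3 admit tertiary general hospitals and their clinicians only. The abstract, the Introduction and 2.1.2 reach to resource-poor areas, resource-constrained settings and healthcare inequality. The comparison meant to bridge the two (2.3.4, 2.4.3, 2.6.1, 2.8.3) is made wholly within tertiary hospitals. This mismatch does not depend on how many of them count as rural.

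**3. How large the rural stratum could be.** The article does not define rural, classify any hospital, or give a number of rural hospitals, clinicians or patients. Only scenarios are possible. Inputs: 218 clinicians and 174 patients per arm (2.5.2); AUC 0.85 against 0.70 and two-sided alpha 0.05 (2.5.1). Assumption: clinicians and patients are spread in proportion to hospitals.

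The variance term in the formula of 2.5.1 is 0.85 × 0.15 + 0.70 × 0.30 = 0.3375. Solved for power with *n* patients per arm:

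power = Φ(0.15 / √(0.3375/*n*) − 1.96)

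| Rural hospitals | Share | Clinicians, total | Patients per arm | Power |
|---|---|---|---|---|
| 0 of 46 | 0% | 0 | 0 | none |
| 1 of 46 | 2.2% | 4.7 | 3.8 | 7% |
| 5 of 46 | 10.9% | 23.7 | 18.9 | 20% |
| 41 of 87 | 47.1% | 102.7 | 82.0 | 65% |

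The last row supposes that every unlisted hospital is rural and every listed one urban. Worked through: √(0.3375/82) = 0.0642; 0.15/0.0642 = 2.34; Φ(2.34 − 1.96) = 0.65. With the 145 per arm before the attrition allowance, that row becomes 145 × 41/87 = 68 per arm and 57% power. Section 2.5.1 plans the whole trial at 0.95, and 2.5.4 at 80% or more.

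The formula is used because it is the plan's own. It takes no account of the number of severe cases or of clustering by clinician or hospital, so the power figures are indicative only.

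**The case against.** The strongest reply is that the documents do not show the rural stratum to be small. That is correct. A reader might infer from the hospital names in Table 1 that almost every site is urban. A city's name in a hospital's title does not prove an urban site, however, and another place name does not prove a rural one. Nor does the shortfall in Table 1 imply an empty stratum: the 41 unnamed hospitals have no stated location and could all be rural.

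A reader might also take 2.1 to mean that only hospitals in prefecture-level cities are eligible. Section 2.1.1 contains no location criterion; 2.1 describes coverage, and 2.1.2 says all eligible hospitals in the province were included.

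Proportional spread is open to challenge too. Sections 2.3.4 and 2.5.3 aim at balanced representation, although they set no quota. The patient figures depend on the total of 348, which sits uneasily with Phase V covering new admissions at all sites. The documents give no proportion of severe cases, so no count of rural severe cases can be derived.

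Finally, tertiary hospitals may differ in resources, so robustness across varying resource levels can be examined to some degree. The abstract's sentence stands in a paragraph that opens with expected results. Both points are fair. They do not rescue inference to facilities below the tertiary tier.

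On Table 1, the text was read from a PDF and should be checked against the published table. All 13 city rows are present, so lost rows are an unlikely explanation.

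**Conclusion.** Two separate defects stand.

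First, eligibility excludes lower-tier facilities, so the planned urban/rural comparison cannot support statements about resource-poor or resource-constrained settings, or the aim of addressing healthcare inequality. This rests on the stated criteria alone.

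Second, Table 1 names 46 hospitals where 87 are claimed, 41 fewer.

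The size of the rural stratum is unknown. In the scenarios above it runs from nothing to 47% of sites. Even at 47%, power within the rural subgroup for an AUC difference of 0.15 is about 65%, assuming proportional spread and the plan's formula. It would be too strong to say that the stratum is nearly empty or that robustness across resource levels cannot be examined at all. The supported conclusion is that the wider generalisation is not backed by the design as written.

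**What to change.** 1. In the abstract, the Introduction and 2.1.2, restrict the hypothesis and conclusions to tertiary general hospitals, and remove the resource-poor and resource-constrained claims.
2. Define rural and classify every listed site before randomisation. Keep urban/rural as a stratum only if enough sites fall in each tier, and state in advance what counts as enough. Otherwise report that subgroup as descriptive. Replacing it with north/south or with case volume would not repair the claim, since neither measures resources and north/south is already a subgroup.
3. Reconcile 87 with Table 1, and correct whichever is wrong wherever the site count is used.

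The cost is some rewording, one classification exercise that must precede randomisation, and a narrower claimed scope. No new sites are needed.

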#### Rationale for multi-center design

2.1.2

The principle of the multicentre design is based on a statistically full sample size as a reference basis. In other words, we included all hospitals in Jiangsu Province that met the study eligibility criteria. This design allows for the establishment of model performance in different Jiangsu regions and in different clinical settings, and ensures general applicability from the statistical principle. Considering the perspective of urban and rural stratification, healthcare resources are generally richer in cities than in rural areas, and we designed it in this way to precisely address healthcare inequality under the geographic factor. [name] concluded that influenza outbreaks have a seasonal element, and the peaks of outbreaks in the northern part of Jiangsu are different from those in the southern part of Jiangsu. This design in a full sample size perspective provides a natural experimental platform for assessing influenza disease observations with seasonal fluctuations. We ensure that the accuracy of the diagnosis will not be affected by the transmission factors of resource differences and geographical differences.

#### Trial registration and reporting standards

2.1.3

This study was registered with the OSF platform (DOI: 10.17605/OSF.IO/SC93Y) and the China Clinical Trial Registry (ChiCTR2000028883). The study protocol was developed following the SPIRIT 2013 guidelines (15). The study phase design we used a visual presentation (Figure 1). This dual registration and standardised reporting framework enhanced the reproducibility of the study.

**Figure 1 fig1:**
[figure not shown]
Study overview. Flowchart illustrating the development and validation of a diagnostic model for early identification of severe influenza. The process involves collecting datasets from 87 hospitals, dividing them for training and validation, and comparing AI and clinician diagnoses. It includes internal and external validation steps, randomization, reader studies, and comparisons between AI-assisted diagnoses and clinician diagnoses, with design change considerations in the prospective validation phase. This figure is drawn by by Figdraw.

#### Phase overview

2.1.4

The study comprises five sequential phases, which is based on the multiple nesting approach used in [name]’s past methods (16–20).

Model development: retrospective data (2019–2024) from 87 hospitals for training and internal validation.External validation-comparative study: benchmarking model performance against clinician diagnoses.Multi-reader, multi-case validation: assessing inter-physician variability with/without model assistance.Randomized controlled trial: evaluating real-time diagnostic accuracy in a clinician-AI collaborative setting.Prospective validation: real-world testing during the 2025 influenza season.

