#### Phase II: external validation-comparative study

2.3.2

The goal of the second phase of the task was to comparatively confirm the diagnostic accuracy of the additional diagnostic assessment using the AI models built in the first phase to assist clinicians in diagnostic assessment. We categorised clinicians into residents, attending physicians and chief physicians according to their experience level. We asked clinicians in the control group to independently judge these influenza cases without the assistance of the AI model; while clinicians in the experimental group did the diagnostic assessment of these influenza cases with the assistance of the AI model. Under this comparison, the metrics of AUC, sensitivity, specificity, and diagnostic consumption time are what are used to initially evaluate the performance of the AI model. Imagine the exciting news that an AI model-assisted clinician can complete a diagnostic assessment with 95% accuracy in just 10 minutes. This dual assessment framework quantifies the added value of AI models in the real world.

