#### Secondary outcomes

2.4.2

Secondary endpoints include diagnostic sensitivity and specificity, defined as the proportion of true severe influenza cases correctly identified by the model or clinicians, which reflects the tool’s capacity to minimize missed diagnoses in high-risk populations (30).

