#### Adjudication of ground truth

2.4.5

To ensure accurate outcome classification, an independent adjudication panel comprising three senior infectious disease specialists will retrospectively review all cases classified as severe influenza, verifying endpoints such as ICU admission, mechanical ventilation, or mortality. Discrepancies in outcome assessments among panel members will be resolved through majority vote, with detailed documentation of dissenting opinions. This rigorous process minimizes misclassification bias and enhances the reliability of outcome data, serving as the gold standard for model and clinician performance evaluation.

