#### Secondary outcomes analysis

2.8.2

Secondary endpoints include diagnostic sensitivity and specificity, calculated using the Clopper-Pearson exact method for binomial proportions to determine the model’s and clinicians’ ability to correctly identify true positive and true negative cases, respectively. Differences between clinician and model performance will be assessed via the Mann–Whitney U test, a non-parametric method suitable for skewed distributions. Positive and negative predictive values (PPV/NPV) will be adjusted for influenza prevalence using Bayes’ theorem and reported with 95% confidence intervals to reflect their clinical utility in real-world settings. The misdiagnosis rate, defined as the sum of false positives and false negatives per 100 diagnoses, will be analyzed using an independent samples t-test (if normally distributed) or Wilcoxon rank-sum test (for non-normal data), quantifying the model’s impact on reducing diagnostic errors. These metrics collectively evaluate the model’s precision, reliability, and practical value in augmenting clinical decision-making.

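### Phase II is defined as a benchmark of the model against clinicians, but section 2.3.2 compares only unassisted with AI-assisted clinicians and labels the result model performance

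*Protocol article*

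**What the plan says.** All references are to the protocol article.

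- **Section 2.1.4 (Phase overview)** gives Phase II this task: "External validation-comparative study: benchmarking model performance against clinician diagnoses". The same list gives Phase III the comparison of reading with and without the model.
- **Section 2.3.2 (Phase II)** states its goal in terms of "using the AI models built in the first phase to assist clinicians in diagnostic assessment". The control group judges the cases unaided, while "clinicians in the experimental group did the diagnostic assessment of these influenza cases with the assistance of the AI model". No reading by the model alone is described.
- The same section says that AUC, sensitivity, specificity and diagnosis time from this comparison "are what are used to initially evaluate the performance of the AI model". It closes with a different description: "This dual assessment framework quantifies the added value of AI models in the real world".
- **Elsewhere**, the article does expect the model to be compared with clinicians. Section 2.8.2 says "Differences between clinician and model performance will be assessed via the" Mann–Whitney U test. Section 2.4.2 defines accuracy as "the proportion of true severe influenza cases correctly identified by the model or clinicians". Section 2.4.5 describes the adjudicated outcome as "serving as the gold standard for model and clinician performance evaluation". None of these three statements names a phase.

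**The concern.** The overview and the procedure give Phase II two different targets. One is the model's discrimination set against that of clinicians. The other is the change in clinicians' discrimination when they can see the model. Section 2.3.2 specifies only the second and then names it as if it were the first.

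Two things follow if the section is carried out as written. First, Phase II reports an effect of assistance, which Phases III and IV are also designed to estimate, and does not report the benchmark that 2.1.4 assigns to it. Second, an assisted clinician's AUC could be read as the model's AUC. That matters because the Significance paragraph of the abstract states its expected result for the model itself, as more accurate than ordinary clinical assessment.

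**Working it through.** The article gives no Phase II figure to reproduce, so the check sets the statements side by side.

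**Step 1. Name the quantities.** On the Phase II cases, let A_M be the AUC of the model's own score, A_U the AUC of unassisted clinicians and A_A the AUC of assisted clinicians.

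**Step 2. Write each section as a contrast.**

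| Source | Contrast |
|---|---|
| 2.1.4, Phase II | A_M − A_U |
| 2.3.2, two groups described | A_A − A_U |
| 2.3.2, sentence on what the metrics evaluate | presented as information on A_M |
| 2.3.2, closing sentence on added value | A_A − A_U, correctly described |

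**Step 3. Ask whether the two contrasts coincide.** Their difference is (A_A − A_U) − (A_M − A_U) = A_A − A_M. This is zero only if assisted clinicians discriminate exactly as the model does, for example by always adopting its score. The plan does not require that. Section 2.3.2 has the model assist, not decide. Sections 2.6.3 and 3.1, written for the intervention groups and for risk mitigation, leave clinicians free to follow, alter or disregard its output. A_A therefore mixes model and clinician. Neither A_A nor A_A − A_U determines A_M, and the gap could have either sign.

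**Step 4. Look for A_M in Phase II elsewhere in the article.**

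- Section 2.3.1 assesses the model's own AUC and sensitivity, but in Phase I internal validation.
- Section 2.3.5 records agreement of the model's predictions with the adjudicated outcome, together with the clinician's diagnosis before seeing the model, but in Phase V.
- The Figure 1 caption lists an AI-versus-clinician comparison and, as a separate item, an assisted-versus-clinician comparison. It names no phase for the first, and the figure itself is not available here.
- Section 2.3.3 says the Phase III model was calibrated in Phase II. This implies that its outputs were set against outcomes there, but 2.3.2 contains no such step.
- Section 2.8.2 tests clinician against model without naming a phase.

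**Result.** The model is evaluated in other phases, and some scoring of it in Phase II is implied. No statement in the article puts A_M − A_U into the Phase II procedure or corrects the sentence that reads the assisted contrast as model performance.

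**The case against.** The strongest reply is that the trial does not lack this evidence. Phase V collects the model's predictions and the clinicians' pre-model diagnoses on the same cases, with an adjudicated outcome, so a model-versus-clinician comparison can be made there. Phase I reports the model's own accuracy. Calibration in Phase II cannot be done without the model's scores, and the Figure 1 caption keeps the two comparisons apart, so the figure may place the stand-alone one in Phase II. A journal article also condenses, and it often says model where it means model-assisted: the introduction's hypothesis speaks of the model, while section 2.5.1 plans the same difference as model-assisted against clinician-only.

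Much of this stands. A reader might infer that the model is never tested on its own, or that the trial has no model-versus-clinician evidence at all. The documents do not support that, for the reasons just given. Nor do they support an inference that the primary result is compromised, because Phase IV is openly a comparison of assisted with unassisted clinicians.

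What does not stand is the defence that this is merely condensed. Section 2.3.2 states a goal, two groups, a set of metrics and what those metrics evaluate. The last of these is wrong for the groups described and conflicts with 2.1.4. Phase V cannot fill the gap in time, because it comes after the model has been used in Phases III and IV. Loose use of the word model explains how the sentence arose, but it leaves the reader with two meanings for the same metrics.

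**Conclusion.** The point holds in a limited form and is minor. Sections 2.1.4 and 2.3.2 disagree about what Phase II compares, and 2.3.2 attributes to the model a result that measures assistance. The extent is one phase of five: its external benchmark and its label. The Phase IV primary comparison and the sample size in section 2.5 are unaffected.

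No size in AUC units can be given, because the article reports no stand-alone model AUC for Phase II and the assisted-minus-unassisted difference does not determine one.

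The conclusion assumes that 2.3.2 will be followed as printed and that assisted clinicians will not simply adopt the model's score. Confidence is medium, because Figure 1 is not available and the calibration remark in 2.3.3 suggests that some model scoring is intended in Phase II.

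**What to change.** - **Add the benchmark to 2.3.2.** Score the locked Phase I model alone against the reference outcome of section 2.4.5, on the same retrospective cases that the unassisted clinicians read. Report the AUC difference between model and unassisted clinicians with a confidence interval.
- **Use a suitable method.** Model and clinicians would be judged on the same cases, and clinicians differ among themselves. The analysis should respect both, for example through the Dorfman-Berbaum-Metz multi-reader framework already planned in sections 2.4.1 and 2.8.1, with the model entered as one fixed reading per case. The Mann–Whitney test of section 2.8.2 treats the two sets as independent and should not be used for this comparison.
- **Relabel the existing contrast.** Say that the assisted-versus-unassisted AUC, sensitivity, specificity and time measure the effect of assistance. The closing sentence of 2.3.2 on added value can stay.

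If the sponsor wants only the assistance contrast in Phase II, rewording 2.1.4 and the sentence on model performance would also remove the conflict, at the price of giving up the benchmark before Phases III and IV.

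The cost is a small extra analysis and some wording. Section 2.7.2 makes Phase II retrospective, and the model's outputs must already exist for the assisted cases, so no new patients or readers are needed.
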